## 2. OBJECTIVES

Primary: To compare immunogenicity (humoral and cellular) induced by PCV10 and PCV13 after the booster dose of a complete vaccination series (3+1, the current NIP schedule)

Secondary:

To compare immunogenicity (humoral) induced by PCV10 and PCV13 at 5, 8, 11 and 12 months of a complete vaccination series (3+1, the current NIP schedule)

To investigate the possible influence of the pneumococcal vaccination on the serological responses of other vaccine components of the NIP which are administered simultaneously in the other limb (DTaP-Hib)

### 3. STUDY DESIGN

Children eligible to receiving the regular vaccinations of the NIP, born after August 2011 (assuring that all children are eligible for and will receive Hepatitis B vaccination)

A controlled, randomized, intervention trial with 2 groups (see figure 2 and table 1).

- Children of group 1 will be invited first (around the age of 1 month), since they have to receive all DTaP-IPV-Hib-HepB and PCV13 vaccinations as part of the trial
  - Vaccinations will be given during home visits
  - Children will be randomized over 2 sub groups in order to diminish the burden of the 8 ml blood sample (which is collected just before or 7-9 days after the 11-months vaccination)
  - For the immune memory, collect 33 children per sub group in order to have 25 evaluable children per sub group (sub group 1a and 1b)
  
- Children of group 2 will be invited around the age of 3.5 months, as to include them in the trial at the age of 5 months
  - Vaccinations are not part of the trial, since they already receive them during well-baby clinic visits
  - Children will be randomized over 2 sub groups in order to diminish the burden of the 8 ml blood sample (which is collected just before or 7-9 days after the 11-months vaccination)
  - For the immune memory, collect 33 children per sub group in order to have 25 evaluable children per sub group (sub group 2a and 2b)

Randomization will be done within group 1 and separately within group 2.

The randomization will not be done for the total study (group 1 and 2 together) since children of the PCV10 group already receive all proper vaccinations in the NIP and randomization would result in a long period between invitation at 1 month of age and inclusion at 5 months of age for the PCV10 group.

Figure 2 Study schedule

[figure not shown]

Blood samples (8 ml) are used for cellular immunogenicity (and 100 ul, of these samples will be used for humoral immunogenicity). Blood samples (100 ul) are used for humoral immunogenicity.

|                                                                                                                               | Group
1a
(PCV13) | Group
1b
(PCV13) | Group
2a
(PCV10) | Group
2b
(PCV10) |
|-------------------------------------------------------------------------------------------------------------------------------|------------------------|------------------------|------------------------|------------------------|
| Invitation (~September 2011)                                                                                                  | x                      | x                      |                        |                        |
| Invitation (~Januari 2012)                                                                                                    |                        |                        | x                      | x                      |
| Receive response card                                                                                                         | x                      | x                      | x                      | x                      |
| Send extra information by email                                                                                               | x                      | x                      | x                      | x                      |
| Telephone call 1 (inquire about the parents interest, explain the study if necessary, make an appointment)                    | x                      | x                      | x                      | x                      |
| Send the extra information also on paper                                                                                      | x                      | x                      | x                      | x                      |
| Check with RCP if child is allowed to receive vaccinations                                                                    | x                      | x                      |                        |                        |
| 2 months vaccination (PCV13 and DTaP-IPV-Hib-HepB)
Including check in- exclusion criteria, signing of IC and randomization | x                      | x                      |                        |                        |
| 3 months vaccination (PCV13 and DTaP-IPV-Hib-HepB)                                                                            | x                      | x                      |                        |                        |
| 4 months vaccination (PCV13 and DTaP-IPV-Hib-HepB)                                                                            | x                      | x                      |                        |                        |
| 5 months blood collection (heel/finger stick)
Including check in- exclusion criteria, signing of IC                        |                        |                        | x                      | x                      |
| 8 months blood collection (heel/finger stick)                                                                                 |                        |                        | x                      | x                      |
| Randomization                                                                                                                 |                        |                        | x                      | x                      |
| Pre 11 months blood collection (8 ml) Questionnaire                                                                           |                        |                        | x                      |                        |
| Pre 11 months blood collection (heel/finger stick) Questionnaire                                                              |                        |                        |                        | x                      |
| Pre 11 months blood collection (8 ml) & vaccination (PCV13 and DTaP-IPV-Hib-HepB) Questionnaire                               | x                      |                        |                        |                        |
| Vaccination (PCV13 and DTaP-IPV-Hib-HepB) Questionnaire                                                                       |                        | x                      |                        |                        |
| Post 11 months blood collection (7-9 days) Questionnaire                                                                      |                        | x                      |                        | x                      |
| 12 months blood collection (heel/finger stick)                                                                                | x                      | x                      | x                      | x                      |
| End of study for participants                                                                                                 | x                      | X                      | x                      | x                      |
| Deliver all samples at the RIVM (after each blood collection visit day)                                                       | x                      | x                      | x                      | x                      |

Table 1 Events during study

## 4. STUDY POPULATION

### 4.1 Population (base)

Children eligible to receiving the regular vaccinations of the NIP, born after August 2011 (assuring that all children are eligible for and will receive Hepatitis B vaccination)

### 4.2 Inclusion criteria

- The children have to be of normal health (same health criteria apply as used in well-baby clinics when a child receives a vaccination, e.g. also children with small increases in temperature ( $\leq 38.5$  °C) or cold are seen as children with normal health)
- The parents/legally representatives have to be willing and able to allow their child to participate in the trial according to the described procedures
- Presence of a signed informed consent (the parents/legally representatives have given written informed consent after receiving oral and written information)
- Group 1: The children are 2 months old ( $\pm 2$  weeks), have not received any vaccinations and will receive all vaccinations (DTaP-IPV-Hib-HepB and PCV13) by the study team
- Group 2: The children are 4-6 months old and have received three DTaP-IPV-Hib-HepB and PCV10 vaccinations according to the 3+1 schedule of the Dutch NIP\*.

*\*The Dutch NIP 3+1 schedule: All children born as of August 1st 2011 will receive Synflorix (PCV10) and DTaP-IPV-Hib-HepB vaccinations, at the age of 2, 3 4 and 11 months of age.*

### 4.3 Exclusion criteria

#### Temporarily exclusion criteria for group 1

- Children that are ill or have a moderate or high fever (rectal temperature of  $> 38.5$  °C). Vaccination will be postponed until the symptoms of illness and the fever have disappeared

#### Exclusion criteria

- Group 1: Previous vaccinations with PCV7 or PCV10
- Group 2: Previous vaccinations with PCV7 or PCV13
- Vaccinations using a schedule that differs from the Dutch 3+1 schedule
- Presence of a serious disease that requires medical care that can interfere with the results of the study

- Known or expected allergy/hypersensitivity against one of the vaccine ingredients (anamnestic, be alert if the child has had medical complaints after previous pneumococcal vaccinations)
- Known or suspected immunological disorder
- Previously administration of plasma products (including immunoglobulin), within three months of study enrolment
- Presence of bleeding disorders
- Communication problems that interfere with the trial
- Prematurity (<37 weeks after gestation)

#### 4.4 Sample size calculation

For **cellular immunity**: each group will contain 25 evaluable children (based on previous experience we expect to include at least 30 children in order to reach 25 evaluable children). The group size is based on the previous KOKKI study (NL24329.000.08).

*'The clinical meaning of differences between the numbers of memory B-cells is still unknown. Therefore power calculations are at the moment not possible. Previous research has shown that the number of memory-B cells circulating in blood is very low before a booster vaccination and in order to observe a trend after revaccination a group of 22 children is needed (including a possible 10% loss of subjects' leads to 25 children for each group).'*

In the KOKKI study, for each child blood was collected at one time point only, being either pre- or 7-9 days post-booster. Inclusion and blood collection was during the same visit. Inclusion in the current study however starts at first vaccination, respectively 9 (group 1) and 6 (group 2) months prior to blood collection for cellular immunity, which can lead to a higher amount of dropout. Taking into account a 10% dropout up to 11 months, we included 33 children in each group. A subsequent estimated failure rate to collect sufficient blood cells of 15% will generate 25 evaluable children.

**Antibody concentrations** will be compared between the PCV10 group of the current study and the PCV13 group of the PIM study (vaccination schedule 2, 3, 4 and 11 months) at 12 months after vaccination. As significance level we take 0.05 two-sided and as power 80%. The expected variance of log(GMC) is 0.27 (this is for serotype 6B, the serotype with the highest variance). Using the following formula  $n = 2k^2\sigma^2 / \delta^2$ , we need 47 children per group to detect a 2-fold difference in GMC (=0.30 difference in log(GMC)) between the two groups. A 2- to 2.5-fold difference is considered to represent a true difference in immunogenicity in this type of study (8,9). To account for 20% dropout, 59

children need to be included per group. As we already include  $2 \times 33 = 66$  children in the cellular immunity part of the study, this group is also large enough to assess antibody concentrations.

The antibody concentrations will be compared for each of the serotypes included in the vaccine. Adjustment for multiple testing is not necessary for these comparisons because the serotypes will not be compared to each other and we are not interested in the overall null hypothesis of no effect (10).

**Antibody concentrations** will also be compared between the PCV13 group of the current study and the PIM study at 12 months after vaccination to bridge the two studies. Using the same sample size calculation as above, we need 59 children in this group as well.

Based on previous experience we expect a participation rate of 5% for all groups.

The study burden for group 1 involves only one 8 ml blood collection, vaccinations and one heel/finger stick (100 ul) Vaccinations are given at home, which parents appreciate. Since PCV13 is a registered vaccine and is not expected to give more side effects as PCV10, we assume that the study burden is perceived as relatively low, especially when the additional protection of three serotypes is taken into consideration.

The study burden for group 2 involves an 8 ml blood collection and 3-4 heel/finger sticks samples. Although the participants have no benefit in this trial, we expect that the heel/finger stick samples will not be perceived as a high burden.

Due to the lack of benefit for the children in group 2, recruitment rates after the first mailings amounted to around 2% instead of 5%.

In order to reach enough inclusions we need to invite approximately 1200 children for group 1 and 3500 children for group 2. We plan to enroll the children of group 1 in one month and the children of group 2 in 3.5 months.

The RCP region Noord Holland - Utrecht will be used and we will assess the exact region based on data from the Dutch Central Bureau for the Statistics (<http://www.cbs.nl>), in the same period of 2010. Due to a hampering recruitment for group 2, the RCP region Noord-Holland-Utrecht recruitment area will be extended with parts of Gelderland and Flevoland.

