### **Humoral immunity**

The aim of **our previous study** (PIM, (NL28918.000.09), 2010-2012), was to assess the optimal PCV vaccination schedule for PCV13, based on humoral immunogenicity after four different vaccination schedules.

An alternative timing and reduction of the number of vaccination doses on the serological response directed against the different serotypes of pneumococci was compared to the currently used\* 3+1 vaccination schedule. The schedules were two 2+1 vaccination schedule (2, 4 and 11 months of age; 3, 5 and 11 months of age) and two 3+1 vaccination schedules (\*2, 3, 4 and 11 months of age; 2, 4, 6 and 11 months of age).

After the start of the study PCV10 was introduced in the NIP and not PCV13. It is therefore important to compare the vaccines for the currently used 3+1 vaccination schedule. Also universal vaccination against Hepatitis B will be introduced for children born after August 2011, and therefore the DTaP-IPV-Hib vaccine will be replaced by DTaP-IPV-Hib-HepB, which could influence the response to PCV13.

**The current study** will investigate the humoral immunogenicity of PCV10 after the currently used 3+1 vaccination schedule (vaccination at 2, 3, 4 and 11 months of age). The data will be compared to the 3+1 vaccination schedule of PCV13 (PIM study). To rule out the influence of the shift from DTaP-IPV-Hib to DTaP-IPV-Hib-HepB vaccine we will use data from group 1 (PCV13) of the current study, to bridge both studies.

As in the PIM study blood samples are collected at one month after the primary series (5 months), at 8, 11 and 12 months of age. The 12 months sample is used to compare the schedules (primary endpoint). The 8 month sample is chosen, since the peak incidence of

IPD is around 8 months. The 5, 8, 11 and 12 month time points are used to assess the kinetics of antibody concentrations in time. To look for interference of concurrent vaccinations DTaP-Hib will be tested.

Hypothesis used for this study:

PCV10 and PCV13 are comparable in inducing cellular and humoral immune responses in Dutch infants. Differences are expected between serotypes; the 7 serotypes of PCV7 are not under influence of natural boosting; the new serotypes present in the vaccines are still under influence of natural boosting.

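### The 12-month bridge to PIM is sized to detect a 2-fold difference, which cannot rule out an influence of the HepB switch, and nothing bridges the 5- and 8-month comparisons

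*Protocol*

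**What the plan says.** **Purpose.** Protocol section 1, under Humoral immunity, compares PCV10 recipients in this trial with PCV13 recipients in the PIM study, who received the older combination vaccine. Group 1 is the link: "To rule out the influence of the shift from DTaP-IPV-Hib to DTaP-IPV-Hib-HepB vaccine we will use data from group 1". The same text accepts that the new combination could affect the PCV13 response.

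**Sizing.** Section 4.4 sets the main antibody comparison (group 2 versus PIM) as follows: "As significance level we take 0.05 two-sided and as power 80" per cent; "The expected variance of log(GMC) is 0.27 (this is for serotype 6B, the serotype with the highest variance"); "we need 47 children per group to detect a 2-fold difference in GMC (=0.30 difference in log(GMC)) between the two groups". It adds that "A 2- to 2.5-fold difference is considered to represent a true difference in immunogenicity in this type of study". Then "To account for 20% dropout, 59" children per group are to be included. For the bridge (group 1 versus PIM, at the 12-month sample) it says: "Using the same sample size calculation as above, we need 59 children in this group as well".

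**Tests.** For concentrations, section 9.1 names an unpaired t test on logs with two-sided p below 0.05, and section 9.2 a t test or a distribution-free alternative. Neither section mentions the bridge. Section 9.1 does report GMCs with 95% confidence intervals. The protocol gives no margin or interval criterion for the bridge.

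**Samples.** The secondary objective (section 2) compares the vaccines at 5, 8, 11 and 12 months. In Table 1 (section 3) the row "8 months blood collection (heel/finger stick") and the corresponding 5-month row are marked for groups 2a and 2b only. Section 4.4 confirms that group 1 gives one 8 ml sample and one stick.

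**The concern.** To exclude an influence is to show that any effect is smaller than some stated amount. That is an equivalence question, answered by where a confidence interval lies. The protocol instead borrows a number from a difference calculation and names only difference tests. If a non-significant group 1 versus PIM result were taken as proof of comparability, a shift of moderate size could pass unnoticed into the PCV10 versus PCV13 contrast, where it would be confounded with the vaccine effect.

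The second part is structural. At 5 and 8 months PIM is the only source of PCV13 data, from another study with a different co-administered vaccine, and group 1 was never scheduled to be bled at those ages. A post-booster result at 12 months says little about comparability after the primary series. The protocol chose the 8-month sample because invasive disease peaks around that age.

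**Working it through.** **Inputs** (all section 4.4 unless noted): two-sided alpha 0.05; power 80%; variance of log10 concentration 0.27, so SD = √0.27 = 0.520; 2-fold = 0.301 on log10; dropout 20%; 66 enrolled per vaccine group. **Assumptions:** the PIM arm is as large as the evaluable group 1 (the protocol does not give its size), and the equivalence margin is 2-fold, the lower end of what section 4.4 calls a true difference.

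**1. The plan's own figure.** n = 2(1.960 + 0.842)² × 0.27 / 0.301² = 46.8, so 47; 47 / 0.8 = 58.75, so 59. Both reproduce. Expected evaluable from 66: 66 × 0.8 = 52.8, about 53.

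**2. What a difference test detects.** SE of the log10 ratio = 0.520 × √(2/n): 0.107 at 47 and 0.101 at 53. Power by the noncentral t distribution:

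| True shift | 47 per group | 53 per group |
|---|---|---|
| 1.5-fold | 37% (non-significant 63%) | 41% (non-significant 59%) |
| 2-fold | 79% | 84% |
| 2.5-fold | 96% | 97% |

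**3. What a non-significant result leaves open at 47 per group.** The 95% CI half-width is 1.986 × 0.107 = 0.213 on log10, so the interval is the estimate times or divided by 10^0.213 = 1.63. A ratio just short of significance (about 1.63) has an upper limit of 1.63 × 1.63, above 2.6-fold and beyond the protocol's own 2- to 2.5-fold threshold. The 95% CI excludes 2-fold only if the observed ratio is below 2 / 1.63 = 1.23.

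**4. Power to show equivalence within 2-fold** (the whole CI of the GMC ratio inside 0.5 to 2.0). At a true ratio of 1 the normal approximation is 2Φ(0.301/SE − z) − 1, with z = 1.645 for a 90% CI and 1.960 for a 95% CI. At 47 with a 90% CI: 0.301/0.107 = 2.81; 2.81 − 1.645 = 1.16; 2Φ(1.16) − 1 = 75%. With t quantiles:

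| Per group | True ratio | 90% CI | 95% CI |
|---|---|---|---|
| 47 | 1 | 75% | 59% |
| 53 | 1 | 81% | 68% |
| 53 | 1.25 | 63% | 49% |

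A tighter margin is out of reach. At 1.5-fold and a true ratio of 1, about 150 evaluable per group would be needed (90% CI, normal approximation).

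**5. Which ages have a bridge** (Table 1 and section 3):

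| Age | Group 1 antibody data |
|---|---|
| 5 months | none |
| 8 months | none |
| 11 months, pre-booster | 1a only (33 enrolled, about 30 after 10% dropout) |
| 7-9 days after booster | 1b only |
| 12 months | 1a and 1b |

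For 30 children in 1a, equivalence power within 2-fold (90% CI, true ratio 1) is 43% against 30 PIM children and 62% against 53. Both PIM sizes are assumed.

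**The case against.** Four points on the other side have force.

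*No pass rule is written down.* A reader might infer that the bridge passes whenever p exceeds 0.05. The protocol does not say so: section 4.4 says only that concentrations are compared, and sections 9.1 and 9.2 do not name the bridge. A margin could sit in an analysis plan that is not shown. This stands, and the point must rest on what the protocol itself fixes: the stated aim, the borrowed number and the sampling schedule.

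*Large shifts would mostly be seen.* A reader might also infer that a failed bridge would usually look like a success. The figures do not support that. Shifts of 2-fold and 2.5-fold, which section 4.4 treats as real, are detected 79-84% and 96-97% of the time. The weakness concerns shifts such as 1.5-fold. These lie inside a 2-fold margin, but a non-significant test does not exclude them.

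*The 12-month endpoint does not depend wholly on PIM.* Groups 1 and 2 both receive the HepB-containing combination and are both bled at 12 months, so a concurrent contrast exists, although section 9.2 names PIM as comparator. The comparisons left without a bridge, at 5 and 8 months, are secondary.

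*The variance is the worst case.* 0.27 belongs to serotype 6B, the most variable. Other serotypes will do better.

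The claim to exclude is also made only for the HepB switch. A wider study effect comes in through the stated wish to bridge the two studies. None of this turns a difference calculation into evidence of no influence, and no analysis plan can supply 5- and 8-month group 1 samples that were never scheduled.

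**Conclusion.** The concern holds in this form. The arithmetic behind 47 and 59 is sound, but it answers a different question from the one the bridge is meant to settle. At the borrowed 47 per group, equivalence within 2-fold has 75% power with a 90% CI or 59% with a 95% CI, not 80%. The 53 expected from planned enrolment bring this to 81% or 68%, but only if the true ratio is 1; at 1.25 the 90% CI figure is 63%. It would therefore go too far to say that enrolment is inadequate, or that a single new target number settles the matter. These figures rest on the 6B variance, an equally large PIM arm and a 2-fold margin. That margin is lenient, because it equals the effect sought in the main comparison.

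At 5 and 8 months no group 1 data exist, so the PCV10-PIM comparisons at those ages rest on an assumption that this trial cannot check. That follows directly from Table 1 and needs no assumption.

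**What to change.** 1. Judge the 12-month bridge for each serotype by the confidence interval of the group 1/PIM GMC ratio against a stated margin no wider than 2-fold, not by non-significance. In section 1, replace the claim to exclude an influence by a statement of what that interval excludes.
2. In section 4.4, say that 59 is sized to detect a 2-fold difference. Add the equivalence power above with its assumptions: true ratio 1, PIM arm equally large, variance of 6B.
3. Where the bridge is not met for a serotype, base the 12-month PCV10-PCV13 comparison on group 1 versus group 2, noting that these groups are not randomised against each other. Without this fallback, dropping PIM would leave the 12-month comparison undefined for that serotype.
4. Label the 5- and 8-month PCV10-PIM comparisons as unbridged and descriptive.
5. Optionally, report 1a versus PIM before the booster at 11 months as supportive only, given its 43-62% power under the assumed PIM sizes.

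Cost: wording and analysis changes, with no extra infants or blood. Some secondary claims become weaker.
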